### 2.6. Genetic Regression of KRAS in an Immunologic Perspective 

The hypothesis on the elimination by the immune system of KRAS mutant clones is under intensive investigation by our and other groups. A complete description of factors involved in the interaction between immune and cancer cells is beyond the scope of this article. However, it has been demonstrated that T cells can recognize peptide epitopes presented by HLA class I on the surface of tumor cells. In fact, DNA mutations can lead to the formation of altered proteins and related peptides absent from the normal proteome. These peptides are called “neoantigens.” Many studies demonstrated that mutation-derived neoantigens can trigger specific tumor clone elimination [71,72,73]. Interestingly, in multiple myeloma, KRAS gene mutations were frequently found in highly immunogenic tumors [74], and, in CRC patients responding to adoptive T-cell therapy, neoantigens derived from mutated KRAS (p.G12D) and presented by HLA-C*08:02 were responsible for CRC cells’ recognition and elimination [75]. “Genetic regression” of KRAS can be hypothesized as an effect of KRAS-mutant neoantigens’ recognition.

## 3. Trial Design

### 3.1. Objectives

#### 3.1.1. Primary Objective

The primary objective is to verify that SRT can induce regression of KRAS mutant clones into the entire metastatic mass in a clean model of oligo-metastatic CRC. 

#### 3.1.2. Secondary Objectives

The most important secondary objective is the description of eventual radiologic responses in non-irradiated disease (abscopal effect). It will be measured through total-body computed tomography (CT) with iv contrast (if contraindicated: chest-computed tomography without iv contrast).

Other secondary objectives are the responses’ duration, progression-free survival (PFS), and toxicity (see beyond for response and toxicity assessment criteria). The response duration will be measured from the time of documented objective response until documented tumor progression. PFS will be determined from the data of treatment start until progression. Overall survival is generally long in this clinical setting so that it cannot be evaluated in the short time of the study. 

#### 3.1.3. Tertiary and Correlative Objectives 

Tertiary and correlative objectives consist in exploratory and descriptive studies of the tumor immune microenvironment in primary tumors, ^18^F-deoxyglucose positron emission tomography (FDG-PET) metabolic responses, HLA repertoire, and immune regulatory cells.

### 3.2. Design and Sample Size Calculation

PRELUDE-1 is a prospective, translational, and proof-of-principle study to detect regression of KRAS mutations in CRC induced by SRT. It will be conducted at the academic hospital Istituto Nazionale Tumori di Napoli, IRCCS “G. Pascale” in Naples (Italy). The sample size of the PRELUDE-1 study is based on the innovative hypothesis that radiation-induced immunity could induce regressive trajectories in metastases bearing KRAS oncogene mutations (i.e., mutKRAS→wtKRAS). 

According to the binomial test, considering a frequency of KRAS mutations of 50.0% (the study is not restricted to KRAS mutated patients) and assuming a probability of mutKRAS→wtKRAS of p_0_ = 0.0077 [9], with α = 0.05, 1-β = 0.60, p = the *a priori* success rate, and X = the number of patients with mutKRAS→wtKRAS, the final sample size is 25 patients. With the algorithm $P\left(X,N,p\right)=\left(\begin{array}{c} N\\ x \end{array}\right)p^{x}{\left(1-p\right)}^{n-x}$, the regressive trajectory is statistically relevant if mutations occurs in >2 out of the planned 25 patients.

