### 3.14. Patients’ Study Withdrawals

Patients’ withdrawals from study will be registered in eCRFs. The information will include the date and the reason for cessation. However, considering the high translational nature, the short duration of the study, its small sample size, and the good safety profile of SRT, withdrawals are expected to be extremely low. Patients off study therapy will be followed-up until death. Patients stopping the treatment early for any reason will not be excluded from the progression-free survival analysis; all patients will be included in the descriptive statistics.

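### The primary test counts all 25 enrolled patients although only the KRAS-mutated half can have the event, and the plan does not say which population its rates and its 60% power describe

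*Protocol article*

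**What the plan says.** The primary objective (section 3.1.1) is to "verify that SRT can induce regression of KRAS mutant clones into the entire metastatic mass". Section 3.2 bases the sample size on it with a one-sample binomial test. On prevalence it says the calculation was made "considering a frequency of KRAS mutations of 50.0% (the study is not restricted to KRAS mutated patients"). The null rate is introduced separately, by "assuming a probability of mutKRAS→wtKRAS of p_0_ = 0.0077 [9"]. The other inputs are "with α = 0.05, 1-β = 0.60, p = the *a priori* success rate". The count being tested is "X = the number of patients with mutKRAS→wtKRAS, the final sample size is 25 patients". No value is given for the a priori success rate. The decision rule is that "the regressive trajectory is statistically relevant if mutations occurs in >2 out of the planned 25 patients"; given the definition of X, I read this as 3 or more patients with regression. The printed formula is the plain binomial probability, with no term for mutation frequency. The eligibility list in section 3.9 has no KRAS criterion. The Abstract repeats p0, alpha, power and the total of 25, and the Discussion (section 4) gives KRAS trajectories as the main reason for the sample size.

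**The concern.** A patient whose tumour is KRAS wild-type at the start cannot lose a KRAS mutation. On the plan's own 50% figure, about half of the denominator of the primary test carries no information on the primary objective. That is workable if every rate in the calculation is defined per enrolled patient, and not if the rates are transition probabilities given a mutation. Section 3.2 lists the 50% and the 0.0077 side by side and does not say whether one was multiplied into the other.

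Two things are at stake. The 60% may describe a power that the enrolled trial does not have, so that a negative result is read as stronger evidence against the hypothesis than it is. And the outcome of the test would move with the KRAS mix that happens to enrol, with no change in the biology.

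**Working it through.** **Inputs (section 3.2).** p0 = 0.0077; alpha = 0.05, sidedness not stated; power 0.60; N = 25; rule X ≥ 3; mutation frequency 0.50. The alternative p1 is not printed.

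**Step 1: the rule at p0 with 25 at risk.**
- P(X = 0) = 0.9923^25 = 0.8243
- P(X = 1) = 25 × 0.0077 × 0.9923^24 = 0.1599
- P(X ≥ 2) = 1 − 0.8243 − 0.1599 = 0.0158
- P(X = 2) = 300 × 0.0077² × 0.9923^23 = 0.0149, so P(X ≥ 3) = 0.0009

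At this p0, 2 events already satisfy alpha 0.05 (or 0.025 in one tail). The written rule is stricter. I therefore carry both cut-offs.

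**Step 2: the stated 60%.** It cannot be reproduced, because p1 is missing. Solving P(X ≥ k | 25, p1) = 0.60 gives the p1 that the 60% would imply with all 25 at risk:
- k = 3 (the written rule): p1 = 0.1215
- k = 2: p1 = 0.0793

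**Step 3: if the rates are per mutated patient.** The chance that an enrolled patient has an event is 0.50 × p1, so X follows Binomial(25, p1/2), which averages over the random number of mutated patients. The last two columns use Binomial(m, p1) with m fixed at 12 or 13.

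| Cut-off | p1 | p1/2 | Power, averaged | m = 12 | m = 13 |
|---|---|---|---|---|---|
| ≥ 3 | 0.1215 | 0.0607 | 19.2% | 17.1% | 20.4% |
| ≥ 2 | 0.0793 | 0.0396 | 26.1% | 24.5% | 27.6% |

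**Step 4: if the rates are per enrolled patient.** Power stays at 60%. The implied rate in mutated patients is p1/0.50: 0.1215/0.50 = 24.3% for the written rule and 0.0793/0.50 = 15.9% for 2 or more. The null per mutated patient is 0.0077/0.50 = 0.0154. Section 3.2 states none of these.

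**Step 5: dependence on who enrols.** The number mutated follows Binomial(25, 0.50), with a central 95% range of 8 to 17, and P(9 or fewer) = 0.115. Under step 4 with the written rule and a 24.3% rate, power given 9 mutated is P(X ≥ 3 | 9, 0.243) = 38%. Given 16 it is P(X ≥ 3 | 16, 0.243) = 79%.

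**Step 6: an exact test on mutated patients only.** Two events is the 0.05 cut-off when P(X ≥ 1) > 0.05 and P(X ≥ 2) ≤ 0.05. That holds for 7 to 46 mutated patients at p0 = 0.0077 and for 4 to 23 at p0 = 0.0154. The likely range of 8 to 17 lies inside both.

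| p0 per mutated patient | False-positive rate, 2 of 12 | 2 of 13 |
|---|---|---|
| 0.0077 | 0.37% | 0.44% |
| 0.0154 | 1.41% | 1.65% |

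Power at a cut-off of 2 with 12 and 13 mutated patients: 25% and 28% for a rate of 8%; 44% and 48% for 12.15%; 60% and 64% for 16%.

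**The case against.** The strongest reply is that section 3.2 says the mutation frequency was considered and, in the same parenthesis, that enrolment is open to all. On that reading the prevalence is already inside a rate per enrolled patient, X out of 25 is a proper binomial count, and no power is lost. The source of p0 is a cited study that is not at hand, so the documents cannot settle this. The reply stands as far as the 60% goes. It does not remove the ambiguity, since the text describes 0.0077 as the probability of the transition and never mentions a product, and it leaves the implied rate of 24% or 16% in mutated patients unstated.

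A reader might infer more: that power in fact falls from 60% to 26%. The documents do not support that. The alternative is back-solved from the stated power, the 26% needs a cut-off of 2 that the plan does not print, and the fall occurs under only one of the two readings. Nor does it help that an exact search with p0 = 0.0077 returns N = 25 for p1 of 0.080 to 0.082 at a cut-off of 2. The same N results whether 0.08 is per mutated patient or is 0.50 × 0.16, and other values of p1 give other sample sizes. That half of 25 is not a whole number matters only if prevalence entered by inflating N.

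Two further replies also stand. The false-positive rate is not at risk: it is 0.09% under the written rule at p0 = 0.0077 and lower still if only half are at risk. And since wild-type patients contribute no events, changing the denominator at a fixed cut-off leaves the decision unchanged. The decision changes because the exact cut-off is 2 rather than 3. Finally, the plan fixes a decision rule and not how the regression rate will be reported, so a two-fold understatement of that rate is a risk of using 25 as denominator, not something the plan commits to.

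**Conclusion.** The concern holds as a defect of definition. The primary test uses all 25 enrolled patients for an event that, by the plan's own figure, about half cannot have, and the plan fixes neither the population of p0 nor any alternative rate. The 60% therefore cannot be read as power for a regression rate in mutated patients. Its size depends on the reading. With rates per mutated patient, power is about 19% under the written rule, or about 26% with 2 or more events. With rates per enrolled patient, 60% stands for a rate in mutated patients of about 24%, or about 16% with 2 or more. These figures assume exactly 50% prevalence, exact binomial tails and a p1 back-solved from the stated power. Under both readings there is an 11% chance that 9 or fewer mutated patients enrol, and the chance of success falls with that number. A definite loss of power is not established.

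**What to change.** In section 3.2 and the Abstract:

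- Make the primary analysis set the patients who are KRAS-mutated before SRT.
- Test exactly on their realised number, with p0 expressed per mutated patient, and say whether that value is 0.0077 or 0.0154.
- Take the cut-off from that exact test. At 12 or 13 mutated patients it is 2 events under either p0, which differs from the written rule of more than 2.
- Report the regression rate with an exact confidence interval on the same denominator.
- State p1 per mutated patient and restate the power from step 6: with 12 to 13 mutated and a cut-off of 2, about 25 to 28% for an 8% rate, 44 to 48% for 12.15%, and 60% or slightly more for 16%.
- Keep all 25 enrolled, with wild-type patients contributing to the other objectives.

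This is a change of wording and analysis set, with no extra patients or procedures. The cost is a less favourable stated power or a larger stated detectable rate.

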### 3.8. Bioinformatics Analysis and Data Presentation

An IlluminaTruSigth Oncology bioinformatics pipeline will be used to analyze DNA sequencing results. Number of reads and coverage in the target regions will be required to be above the manufacturer’s suggested thresholds. Sequence data will be aligned to the human reference genome GRCh37 (http://www.ncbi.nlm.nih.gov/projects/genome/assembly/grc/human/index.shtml) (accessed on 22 June 2021) through the Burrows–Wheeler Aligner with default parameters [78]. GENCODE, ICGC-PCAWG, dbNSFP, COSMIC, ClinVar, CancerMine, 1000Genomes, OncoScore, CIViC, and CBMDB databases will be used to assess the clinical significance of the found variants. The global minor allele frequency cut-off to filter and remove variants will be <1%. The four-tiered structure, designed by the joint consensus recommendation of the AMP/ACMG [79] will be applied to prioritize variants. However, to exclude residual false positives, variants will be also manually curated. The overall genetic evolution will be indicated with: (i) the percent of mutational concordance between different samples and (ii) Venn diagrams in order to plot intersections among genetic results in different samples (see beyond). Phenolyzer, a computational tool that prioritizes genes on the basis of updated existing knowledge (protein–protein interactions, the sharing of biological pathways or gene families, gene–gene transcriptional regulation, etc.), will be used to evidence relevance and relationships between any “seed” genetic variants and “secondary” ones [80]. 

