### 3.11. Timing of Exams and Procedures

Timings and types of procedures are synthesized in Figure 1 and Table 1.

Screening phase. Inclusion and exclusion criteria will be evaluated during the screening phase.

Baseline phase. Thereafter, after signing the informed consent, a venous blood sample (10 mL) for the liquid biopsy (LB) will be collected coinciding with the routine assessment before the SRT start. Baseline visit (clinical history, clinical examination, PS ECOG, vital signs) and exams (including basal LB (LB-T1)) will also be carried out within 14 days before the SRT start. Blood count and clinical biochemistry will be performed at our local laboratories. The following parameters will be assessed: blood count with leukocyte formula, hemoglobin, platelets, total bilirurbin, AST, ALT, alkaline phosphatase, serum creatinine, total proteins, sodium, potassium, calcium, urea, lactic dehydrogenase, creatinine clearance, CEA, and CA19.9. Patient’s heart rhythm and conduction will be evaluated with ECG. The ventricular ejection fraction will be assessed with cardiac ultrasonography.All potentially childbearing women musthave a negative pregnancy test during the screening phase. If requested by the local ethics committee, the test can also be repeated during treatment. Barrier methods for anti-conception must be used by all patients throughout the duration of the study. FDG-PET and total-body computed tomography with iv contrast or, if contraindicated, magnetic resonance (MRI) abdomen and high-definition chest-computed tomography without iv contrast will be performed. 

Treatment phase. Clinical examination and evaluation of vital signs will be performed at each radiotherapy visit. Cardiological evaluation, CEA, CA19.9, and assessment of response to treatment will be performed after 40 days and 2 months from the radiotherapy start and, thereafter, every 3 months until progression. 

“Interval” phase. LB-T2 will be performed 40 days after major nodule irradiation coinciding with post-RT cell blood count and biochemical assessment along with CT total-body-scan and FDG-PET. Thereafter, the disease will be monitored every three months, and non-irradiated nodules will be treated in case of volumetric progression according to clinical practice in oligo-metastatic disease.

End-of-study phase. The study ends after LB-T2 assessment. 

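### The null rate for the primary KRAS regression count comes from tissue pairs and makes no allowance for a mutation missed in one plasma draw, so detection noise can exceed it when plasma signal is low

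*Protocol article*

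**What the plan says.** Section 3.2 of the protocol article bases the primary test on a per-patient binary change, "X = the number of patients with mutKRAS→wtKRAS". The null probability is 0.0077, cited to the group's earlier study. Patients are not selected on KRAS: "considering a frequency of KRAS mutations of 50.0% (the study is not restricted to KRAS mutated patients". The rule is that "the regressive trajectory is statistically relevant if mutations occurs in >2 out of the planned 25 patients".

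Section 2.5 describes the earlier study as a comparison of KRAS status in FFPE metastases and FFPE primaries, and defines regression as loss of the alteration from primary to metastasis.

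Section 3.11 and Table 1 give one liquid biopsy before SRT (LB-T1) and one after: "LB-T2 will be performed 40 days after major nodule irradiation". The study ends with that second sample. Section 3.4 also provides for DNA from the FFPE primary, which section 3.9 requires to be available.

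On call quality, section 3.8 says "Number of reads and coverage in the target regions will be required to be above the manufacturer"'s suggested thresholds. It adds a population-frequency filter and manual curation aimed at false positives. The article states no rule for what makes a post-SRT sample wild type.

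**The concern.** In this endpoint the damaging error is a false negative. If KRAS is missed at LB-T2, the patient is scored as a regression. The safeguards stated in section 3.8 work against false positives, apart from the minimum for reads and coverage. That minimum does not ensure that enough tumor DNA was in the tube.

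A null rate observed between tissue blocks says nothing about how often an unchanged plasma mutation is missed on a second draw. If that happens more often than 0.77% per patient, the binomial test is run against too low a null. A positive result could then reflect non-detection, yet it would be read as support for the primary objective in section 3.1.1, that SRT induces regression of KRAS mutant clones.

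**Working it through.** **Inputs from the article (section 3.2).** N = 25, p0 = 0.0077, KRAS mutation frequency 0.50, rule X > 2.

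**The plan's own figures.** N = 25 with power 0.60 cannot be reproduced, because no numerical alternative rate is given. The rule can be checked at p0:
- P(Bin(25, 0.0077) ≥ 3) = 0.0009.
- P(Bin(25, 0.0077) ≥ 2) = 0.0158, so a cut-off of 2 would already meet α = 0.05.

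The stated rule is therefore strict. Solving P(Bin(25, a) ≥ 3) = 0.05 gives a = 0.0335, which is 0.0335/0.0077 = 4.4 times p0. Noise below that rate leaves the error under 5%.

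**Check 1: common detection probability s per draw (assumed).** There is no true change, and the draws are independent. The spurious loss rate per enrolled patient is:
- 0.5 × s × (1 − s) if LB-T1 defines mutKRAS;
- 0.5 × (1 − s) if the FFPE primary does.

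| s | LB-T1 defines: rate, P(≥3 of 25) | FFPE defines: rate, P(≥3 of 25) |
|---|---|---|
| 0.80 | 0.080, 32% | 0.100, 46% |
| 0.90 | 0.045, 10% | 0.050, 13% |
| 0.95 | 0.024, 2.1% | 0.025, 2.4% |
| 0.98 | 0.0098, 0.2% | 0.010, 0.2% |
| 0.985 | 0.0074, 0.08% | 0.0075, 0.09% |

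At the upper end, noise drops below p0 once s is above about 0.984 under either reading. The error stays under 5% once s is above about 0.93.

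**Check 2: signal varying between patients (assumed).** Mutant molecules per draw are Poisson with mean λ = median × exp(SD × Z), where Z is standard normal. The mean is the same at both draws. A call needs at least k molecules, and s(λ) = P(Poisson(λ) ≥ k). With LB-T1 defining mutKRAS, the rate per enrolled patient is a = 0.5 × E[s(λ)(1 − s(λ))], and the chance of meeting the rule is P(Bin(25, a) ≥ 3). The grid is SD 1.0 and 1.5 by k = 1, 2, 3 and 5.

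| Median molecules | a | P(>2 of 25), no effect |
|---|---|---|
| 5 | 0.024 to 0.049 | about 2% to 12% |
| 10 | 0.009 to 0.036 | 0.1% to 6% |
| 50 | 0.0002 to 0.010 | at most 0.2% |

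Worked line: median 5, SD 1.0, k = 3. The share called at LB-T1 is 0.717, and 0.136 of those are lost at LB-T2. So a = 0.5 × 0.717 × 0.136 = 0.049, and P(≥3 of 25) = 12%. If the FFPE primary defines mutKRAS in the same scenario, a = 0.5 × (1 − 0.717) = 0.14 and P(≥3 of 25) = 71%.

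At a median of 10, only one of the eight grid points passes 5%.

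**The case against.** The best counter-argument is that the effect depends on a plasma signal level the article does not give, and that the rule is strict enough to absorb a good deal of noise. Both parts stand. Exceeding p0 is not the same as breaking the test, and at high signal nothing happens. Call limits and assessability rules may also sit in a full protocol or laboratory procedure, so their absence from an article is not in itself a fault. That does not rescue the null rate: an assay manual cannot turn a tissue-pair frequency into a plasma repeat-draw frequency.

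Three stronger readings are tempting and are not supported:
- **A patient qualifies and regresses by crossing the same detection limit twice.** The article states no limit and does not say that LB-T1 defines mutKRAS. Section 2.5 points to the primary tumor.
- **Noise is well above p0 as a fact.** This holds only for low signal, which is an assumption.
- **The false-positive chance reaches 36% with 12 mutant patients.** That figure applies a loss rate among LB-T1-positive patients (up to about 18%, at median 5 and k = 5) to all 12 expected mutKRAS patients. In that scenario only about 53% of mutKRAS patients are positive at LB-T1, so 12 positives would need about 12/0.53, or 22 to 23, mutKRAS patients among 25. The article expects half.

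**Conclusion.** The point holds in a conditional form. Section 3.2 tests a single before/after plasma change against a null rate cited to a tissue comparison, and does not fix which sample makes a patient mutKRAS. If LB-T1 does, noise alone can exceed p0 at low signal. The no-effect chance of meeting the rule is then about 2% to 12% at a median of 5 molecules, falling to at most 0.2% at 50, against 0.09% at p0. If the FFPE primary does, spurious losses are more frequent.

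These figures rest on Poisson draws, unchanged shedding, 50% mutKRAS, log-SD 1.0 to 1.5 and a call limit of 1 to 5 molecules. None of these except the 50% comes from the article. The rule keeps its error under 5% until noise passes about 0.0335 per enrolled patient. This should be corrected before analysis, but it does not show that the test fails.

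**What to change.** In section 3.2:

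1. State which sample defines a mutKRAS patient at risk, and count a regression only where KRAS was detected at LB-T1.
2. Report wtKRAS→mutKRAS changes from LB-T1 to LB-T2 beside the losses. With unchanged shedding, each has probability 0.5 × s × (1 − s) per enrolled patient, so gains estimate the noise from the trial's own data.
3. Do not claim SRT-induced regression unless losses exceed gains.
4. Add a sensitivity count limited to patients whose LB-T1 signal is clear of the assay's call limit.

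Step 3 is a necessary condition and not a full correction. In a trinomial with 25 patients and loss and gain both at 0.045, P(losses ≥ 3 and losses > gains) is 9.4%, against 10.0% for losses ≥ 3 alone. The gain count and the sensitivity count must therefore be read with the test.

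A fixed margin, such as 10 molecules at LB-T1, should not be the primary rule. At a median of 5, only 27% to 34% of mutKRAS patients reach it, which is 12.5 × 0.27 to 12.5 × 0.34, or about 3 to 4 patients.

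The cost is wording and reporting; both samples are already planned. LB-T1-negative patients no longer count as at risk, so the power of the >2 rule should be restated. True progressive changes would make the comparison with gains slightly conservative.
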